### D2 Study design

The D2 study is a single center, observational, longitudinal, case-control study. One hundred and sixty-eight adult patients, aged greater than 50 years with type 2 diabetes will be followed: 50% with LVH (case) and 50% without (control). Patients will be assessed at baseline (0 months) and will return for tests at the 24 month time-point. Based on recruitment in our other diabetes, cognitive and imaging trials, it is expected that 80–90 patients will be recruited annually for the first 2 years. Recruitment of new patients will be completed at the end of 2 years, allowing the next 2 years for follow-up.

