### Sample size

We aim to recruit 168 patients with type 2 diabetes. Patients will be divided based on the presence of LVH. Higher left ventricular mass and concentric geometric changes have been demonstrated in approximately 35–40% of patients with type 2 diabetes [16, 17]. Our data suggested more than 50% of participants will have LVH [18]. We calculated our sample size in order to include sufficient participant numbers for both the primary endpoint comparison (brain volume) and for the primary outcome measure (presence of cognitive impairment). The primary endpoint requires a direct comparison of two groups: type 2 diabetes patients with LVH and those without. We based our effect size on published brain volume and cortical thickness estimates performed on healthy controls, cerebrovascular disease patients and Alzheimer’s disease patients [40–42], and prior imaging of healthy controls and stroke patients performed by our group [43]. We use an average brain volume change of <0.5% per annum for controls, 1–2% for cerebrovascular disease, and 2–4% for dementia [44].

We used a modified retrospective case-control method. All participants have the exposure (type 2 diabetes), which will naturally halve by the additional risk factor (LVH, expected prevalence around 50%), but only some of them will develop the primary outcome (cognitive decline). We used an ANCOVA method to estimate sample size for four samples (cognitively impaired LVH, non-cognitively impaired LVH, cognitively impaired non-LVH, non-cognitively impaired non-LVH) with repeated measures, including a correlation score between baseline and follow-up. Using alpha = 0.05 (two-sided), power = 0.8 and an estimated correlation of 0.1, we estimated that 140 (i.e., 35 in each of 4 groups) participants will be required. Given we expect around 20% attrition due to death or non-participation (unable to participate in testing due to new pacemaker/implanted metal/other medical issue, lost to contact, no longer interested), we have estimated a total recruitment number of 168. This model has used the conservative estimates from these results and assumes the following: that 30% of patients will be cognitively impaired at 2 years; a 1% total annual brain volume change for patients with type 2 diabetes; that 30% of patients will exhibit specific left ventricular geometric changes; and a low correlation between baseline and follow-up measures.

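### The sample size assumes four equal LVH-by-impairment cells of 35, but the plan's own 30% impairment rate gives about 21 and 49, so the stated 80% power does not carry over to contrasts that use impairment status

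*Protocol article*

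**What the plan says.** All of the sizing is in one section of the protocol article, Sample size.

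- The model is an ANCOVA for "four samples (cognitively impaired LVH, non-cognitively impaired LVH, cognitively impaired non-LVH, non-cognitively impaired non-LVH) with repeated measures".
- Its settings are given as "Using alpha = 0.05 (two-sided), power = 0.8 and an estimated correlation of 0.1".
- Its result is "we estimated that 140 (i.e., 35 in each of 4 groups) participants will be required". This is raised to 168 for an expected attrition of around 20%.
- The assumptions listed at the end of the section include "that 30% of patients will be cognitively impaired at 2 years".
- On LVH, the section gives "LVH, expected prevalence around 50" per cent, and the D2 Study design section fixes the split as "50% with LVH (case) and 50% without (control").
- The section also says: "The primary endpoint requires a direct comparison of two groups: type 2 diabetes patients with LVH and those without". It adds that the sample must serve the cognitive impairment outcome as well.

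The Statistical analysis section compares LVH with no LVH under hypothesis 1, and impaired with normal participants at 2 years under hypothesis 2. It specifies no contrast between individual LVH-by-impairment cells.

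**The concern.** Two figures in one paragraph cannot both hold. Four equal cells require half of the participants to be impaired at 2 years, and the listed assumption is 30%. LVH status is known at baseline and can be balanced by recruitment. Impairment at 24 months is an outcome. The Eligibility criteria section does not enrich for it, and it excludes known dementia. The impaired cells will therefore be smaller than the calculation needs, and nothing in the plan can fill them.

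At stake is how the co-primary outcome is read. Cognitive decline at 2 years is co-primary, and the first analysis under hypothesis 2 compares impaired with unimpaired participants. A null result there would be judged against a stated 80% that belongs to a layout the study is not expected to have.

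**Working it through.** **Inputs.** From Sample size: two-sided alpha 0.05, power 0.80, 140 required as 4 × 35, 30% impaired, LVH about 50%, attrition about 20%, 168 recruited. No SD and no difference between cells is stated.

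**Reproducing the plan's figures.** 4 × 35 = 140 and 140 × 1.2 = 168. The 35 per cell cannot be derived. With correlation 0.1, a 1-point difference gives 35 per group only if the SD is chosen to fit: 1.49 (follow-up value only), 1.50 (ANCOVA variance, 1 − 0.1²) or 1.11 (change score, 2(1 − 0.1)).

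**Cell sizes.**

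- Implied by equal cells: 70/140 = 50% impaired.
- Impaired cell at 140 completers: 140 × 0.5 × 0.3 = 21.
- Unimpaired cell at 140 completers: 140 × 0.5 × 0.7 = 49.
- At the stated attrition: 168 × 0.8 = 134.4 completers, so about 20 per impaired cell and 47 per unimpaired cell. Pooled, this is about 40 v 94.
- All 168 with no attrition: 168 × 0.15 = 25.2 per impaired cell, still below 35.

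The 21 is the average of the two impaired cells. If impairment were 40% with LVH and 20% without (an assumption averaging 30%), they would be 28 and 14.

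**Relative power.** Each contrast is given the standardised difference d that has 80% power under the equal split, and power is then recomputed at the expected sizes. In the normal approximation, d = 2.80 × √(1/n₁ + 1/n₂) at the equal split, and power = Φ(d/√(1/m₁ + 1/m₂) − 1.96) at the expected sizes m₁ and m₂.

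*Pooled impaired v unimpaired (hypothesis 2).* Equal split 70 v 70: d = 2.80 × √(2/70) = 0.474 (0.477 with the t distribution).

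- 42 v 98: √(1/42 + 1/98) = 0.1844; 0.474/0.1844 = 2.57; Φ(0.61) = 73%.
- 40 v 94: √(1/40 + 1/94) = 0.1888; 0.474/0.1888 = 2.51; Φ(0.55) = 71%.

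*Impaired LVH v impaired non-LVH (not a planned analysis).* Equal split 35 v 35: d = 2.80 × √(2/35) = 0.670 (0.679 with t).

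- 21 v 21: √(2/21) = 0.3086; 0.670/0.3086 = 2.17; Φ(0.21) = 58%.

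The noncentral t gives the same figures to within a percentage point. The two calculations rest on different values of d, because each contrast is set to 80% at its own equal split. They are two separate scenarios. At d = 0.68, the pooled 42 v 98 contrast would have about 95.5% power.

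*LVH v no LVH (primary).* At 140 completers this is 70 v 70 whatever share is impaired, so the 30% rate does not change its power.

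**Detectable d at 80% power, two-sample t-test, about 134 completers.**

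| Contrast | Sizes | d |
|---|---|---|
| LVH v no LVH | 67 v 67 | 0.49 |
| Impaired v unimpaired | 40 v 94 | 0.53 |
| LVH v no LVH among impaired | 20 v 20 | 0.91 |

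**The case against.** The best defence is that the four cells appear only in the sizing model. The planned analyses are the LVH comparison, which is untouched, and the pooled impairment comparison, which loses 7 points at 140 completers. If the 80% was meant for pairwise cell contrasts at d = 0.68, both planned comparisons have ample power: about 98% at 70 v 70 and 95.5% at 42 v 98. With no SD, effect or target contrast stated, absolute power cannot be known, and a t-test only approximates the repeated-measures ANCOVA described. All of this stands, and it limits the point to contrasts that use impairment status and to relative losses. It does not reconcile 50% with 30%, and the section attaches its 80% to the four-cell model and reports no power for any other comparison.

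Three stronger readings are tempting, and the document does not support them.

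- *The study as a whole misses 80% power.* The primary comparison does not depend on the impairment split.
- *LVH will be scarce, which unbalances the cells further.* The section does say "Higher left ventricular mass and concentric geometric changes have been demonstrated in approximately 35–40% of patients with type 2 diabetes", but that describes higher mass and concentric geometry. Its next sentence expects LVH in more than half of participants, and the design sets a 50/50 split.
- *The low power among impaired participants defeats a planned analysis.* The 58% belongs to a contrast that the Statistical analysis section does not specify.

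**Conclusion.** The equal-cell statement contradicts the 30% assumption, and the sample-size basis is wrong as written. The expected layout at 140 completers is 21/49/21/49, against the stated 35 in each cell. For the planned pooled impairment contrast, an effect with 80% power under the equal split has about 73%, or about 71% after the stated attrition. The unplanned contrast between the two impaired cells would have about 58%.

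These sizes assume 30% impaired, LVH at 50%, a simple two-sample comparison, and an effect back-calculated from 80% power because the plan states none. The direction of the loss does not depend on the effect size, since only the group sizes change. This is a fault in the stated justification, of moderate size for the co-primary analysis. It calls for no change to the endpoints or to the planned analyses.

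**What to change.** Keep enrolment at 168. In Sample size, delete the statement that 35 are needed in each of four groups. Restate the basis at about 134 completers, which is 168 less the stated 20% attrition, as detectable standardised differences at 80% power from a two-sample t-test:

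- LVH v no LVH, 67 v 67: d about 0.49, as the basis for the primary endpoint.
- Impaired v unimpaired, 40 v 94: d about 0.53, for hypothesis 2.
- Any LVH contrast among impaired participants, about 20 v 20: d about 0.91, labelled exploratory.

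State that the impaired group sizes are expectations under the 30% assumption.

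The cost is a rewritten paragraph and a less favourable stated power for impairment-based contrasts. No extra participants are needed. Holding to 35 per impaired cell instead would take 35/(0.5 × 0.3), about 233 completers, and no planned analysis requires that.

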**Methods:**

The D2 study is a single centre, observational, longitudinal case control study that will follow 168 adult patients aged >50 years with type 2 diabetes: 50% with LVH (case) and 50% without LVH (control). It will assess change in cardiovascular risk, brain imaging and neuropsychological testing between two time-points, baseline (0 months) and 24 months. The primary outcome is brain volume change at 24 months. The co-primary outcome is the presence of cognitive decline at 24 months. The secondary outcome is change in left ventricular mass associated with brain atrophy and cognitive decline at 24 months.

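### The 20% attrition allowance was added to the 140 required instead of divided out, so 168 recruits leave about 134 completers

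*Protocol article*

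**What the plan says.** The Sample size section of the protocol article builds its recruitment figure in three steps.

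- **Requirement.** "Using alpha = 0.05 (two-sided), power = 0.8 and an estimated correlation of 0.1", the section concludes: "we estimated that 140 (i.e., 35 in each of 4 groups) participants will be required".
- **Losses.** "Given we expect around 20% attrition due to death or non-participation". The reasons listed are death, a new pacemaker or other implanted metal, other medical problems, loss of contact and loss of interest.
- **Result.** "we have estimated a total recruitment number of 168".

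The same section opens with that total: "We aim to recruit 168 patients with type 2 diabetes". The Abstract (Methods) says the study "will follow 168 adult patients aged >50 years with type 2 diabetes", and the sections on the D2 study, D2 Study design and Study outcome measures use 168 as well. The article gives no other attrition rate and no other basis for 168.

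On timing, D2 Study design says: "Patients will be assessed at baseline (0 months) and will return for tests at the 24 month time-point". Under Study outcome measures, the primary endpoint is change in brain volume at 2 years.

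**The concern.** Attrition is a fraction of the people enrolled. To finish with a given number after losing a fraction *d*, that number must be divided by (1 − *d*). Multiplying it by (1 + *d*) gives too few, and the gap widens as *d* grows. The recruitment total here is what the multiplication gives.

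The 140 has to mean people with both assessments. The primary endpoint is a change between baseline and 24 months, so a participant who does not return has no change score. All the listed reasons for loss act after enrolment. The 20% therefore has to come off the 168, and what remains falls below the stated requirement.

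At stake is whether the planned recruitment delivers the stated 80% power under the protocol's own attrition assumption. Readers will take 168 as a number that already covers the expected losses.

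**Working it through.** **Inputs, all from the Sample size section:** required number 140 (4 × 35); two-sided alpha 0.05; power 0.80; expected attrition 20%; recruitment target 168.

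**1. Reproduce the plan's figure.**
- Multiplying: 140 × (1 + 0.20) = 168. This matches exactly.
- Dividing: 140 / (1 − 0.20) = 175. This does not match; the difference is 7 recruits, and 7/168 = 4.2%.

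**2. Completers from 168 recruits.**
- 168 × 0.80 = 134.4, so about 134, which is 6 below 140.
- Spread evenly over the four planned groups, 134.4 / 4 = 33.6 per group against 35. This is a nominal average only.

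**3. Attrition that 168 can absorb.**
- 1 − 140/168 = 28/168 = 16.7%.

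| Attrition | Completers from 168 | Recruits needed for 140 |
|---|---|---|
| 15% | 142.8 | 164.7 |
| 16.7% | 140.0 | 168.0 |
| 18% | 137.8 | 170.7 |
| 20% | 134.4 | 175.0 |
| 22% | 131.0 | 179.5 |

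**4. Effect on power.** The article gives an assumed change, "a 1% total annual brain volume change for patients with type 2 diabetes", but no standard deviation or standardized effect, so the 140 cannot be re-derived. I therefore assume an effect that is just detectable with 80% power at 140, and scale it. With the allocation between groups held fixed, the standardized difference is proportional to the square root of the sample size.
- At 140 the standardized difference is 1.96 + 0.84 = 2.80.
- At 134.4 it is 2.80 × √(134.4/140) = 2.80 × √0.96 ≈ 2.745. Then 2.745 − 1.96 = 0.785, and the normal probability below 0.785 is 0.784.
- At 134 the same calculation gives 0.783.

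Power is therefore about 78%, a loss of a little under 2 percentage points. Two further checks, each fixed to give 80% at the planned size, agree: a two-sample t-test with 35 per group (standardized difference 0.679) gives 0.783 at 33.6 per group, and a four-group F test (f = 0.283) gives 0.781 at a total of 134. Both effect sizes are back-calculated assumptions, not figures from the article.

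**5. Feasibility of 175.** D2 Study design expects 80 to 90 recruits a year for 2 years, which is 160 to 180. A target of 175 needs 87.5 a year.

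**The case against.** The arithmetic itself is hard to dispute. The case on the other side is about how much it matters and what should be written in its place.

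- **The rate is approximate.** The text says around 20%, and 168 suffices at 16.7%. This stands as a reason to call the consequence small. It does not rescue the sentence: the exact match to 140 × 1.20 shows that 20% was the working figure, and at that figure 168 falls short.
- **A power of 78% rests on an unverified 80%.** No standard deviation is given, and the equal groups of 35 sit badly with the section's other assumptions. With 30% impaired at 2 years, 140 completers include 42 impaired participants. If LVH splits the cohort evenly and impairment is equally common in both halves, the groups hold about 21 impaired and 49 unimpaired each. This stands as a limit on the claim: 33.6 per group is only an average, and 78% is no more reliable than the 80% it is scaled from. The loss of about 2 points does not need equal groups, only that the allocation stays the same when the total falls.
- **The power models are not the planned ANCOVA.** This is true, and it is why the back-calculated effect sizes are labelled as assumptions. The scaling gives much the same answer in each model tried.
- **175 is near the top of the recruitment range and does not divide evenly.** This stands. At 80 a year even 168 is not reached, and 175 splits neither into halves nor into four equal groups; 35 / 0.80 = 43.75, rounded up to 44 per group, gives 176. It is a reason to prefer restating the sentence over raising the target.

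**Conclusion.** The point holds. The attrition allowance was applied to the wrong base. At the stated 20%, 168 recruits give about 134 completers, 6 fewer than the 140 the protocol says it requires; 175 recruits would be needed.

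The completer count, the 175 and the 16.7% threshold follow from the article's own figures. The fall in power from 80% to about 78% also assumes that 140 does give 80% and that the split between groups does not change. This finding does not confirm the 140 itself.

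The shortfall is small and does not threaten the study. It should still be corrected, because the stated link between recruitment, attrition and power is wrong as written.

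**What to change.** Keep 168 and replace the attrition sentence in the Sample size section with wording such as: *With 168 recruited and 20% attrition, about 134 participants will complete; if 140 completers give 80% power, 134 give about 78%. The target of 140 is reached if attrition does not exceed 16.7%.* The other sections that state 168 then need no change.

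The cost is one sentence and a slightly less favourable power figure. Recruitment, budget and participant burden are unaffected.

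If the sponsor prefers to protect 140 completers at 20% loss, the target becomes 175 (176 for four equal groups). That lies within the expected 160 to 180 but needs recruitment close to the upper end, and 168 would have to be changed wherever it appears.

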### Statistical analysis

The analysis of this study will be performed in three parts as follows.
***Hypothesis 1: comparing brain volumes between participants with and without LVH***. Independent samples t-tests will be used to determine differences between participants with and without LVH at each time-point. Repeated-measures t-tests will be used to determine the extent of brain volume loss across the two time-points. These results will be compared between groups. In the cortical thickness analyses, the large number of statistical inferences being carried out across the cortical sheet (approximately 160,000 vertices per hemisphere) requires adjustment of the statistical threshold. This is to control for the increased number of false positive findings using false discovery rate correction procedure widely used for cortical thickness analyses. In the volumetric analyses, total brain volume, regional white matter, cortical and subcortical volume changes will be modelled using a repeated measures design. Intracranial volume, which is determined partially by gender and race, is a known confounding factor that contributes to regional brain volumes. This will be controlled for in the statistical analysis of regional brain volume change. We have demonstrated this to be a reliable index of brain volume in previous studies [43].
***Hypothesis 2: correlating brain volume with cognitive performance.*** The initial regressive analysis will examine differences between cognitively impaired and normal participants at 2 years. We will correlate both global and regional measures of brain volume with the groups. Global brain and regional hippocampal volumes, and mean regional cortical thickness values for the stated regions of interest will be compared between two groups, in order to correlate LVH-associated brain volume changes with cognition. We will also perform a multivariate analysis across the cohort as a whole to investigate whether there is a dose-related association with any extent of cardiac impairment. Multivariate regression will be conducted to determine whether brain volume loss correlates with the presence or absence of cognitive impairment, adjusting for known important variables such as age, years of education, CIMT, atrial fibrillation, cholesterol and hypertension, as well as potentially relevant variables including *APOE* ε4 status, cardiac indices such as stroke volume, renal function and HbA_1c_ levels.
***Hypothesis 3: comparing brain volume and cognitive performance in participants with increased left ventricular mass and specific left ventricular geometric patterns.*** Analysis will be similar to that for LVH, except that patients will be divided on the presence or absence of specific morphometric measures. That is, analyses will be performed at each time-point (cross-sectional), and also longitudinally, to investigate change across time. Repeated-measures t-tests will determine the extent of brain volume loss across the two time-points and compared between groups. Correlation with cognitive performance will be performed as above. Unadjusted differences for clinical variables between groups will be assessed by *t*-test. Difference in laboratory data and left ventricular systolic function will be adjusted for age and sex by use of ANCOVA. Differences in left ventricular structure and geometry will be adjusted for age, sex, BMI, and systolic blood pressure as their major established covariates with further adjustment for duration of hypertension. Fisher’s Exact Test and odds ratios will be used to test differences for categorical variables. Logistic regression analysis will be used to derive odds ratios adjusted for covariates. Multiple regression analyses will be performed to assess relation of cognitive and brain volume measures to higher left ventricular mass independent of established covariates and duration of hypertension.

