### Study outcome measures

Our primary endpoint is brain volume change at 2 years (hypothesis 1). Our co-primary outcome is the presence of cognitive decline at 2 years (hypothesis 2). We shall use advanced brain imaging to accurately measure brain volume and correlate this with cardiac echocardiography, carotid intima media thickness (CIMT), and 24 h blood pressure and ECG monitoring in 168 patients with type 2 diabetes, with longitudinal testing allowing measurement of change at 24 months. Concurrent neuropsychological testing will indicate whether the clinical profile of cognitive impairment and dementia aligns with measures of brain volume.

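### Hypothesis 1 lists several brain-volume analyses but names none as the test of the LVH difference in two-year change, and none matches the ANCOVA used for sizing

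*Protocol article*

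**What the plan says.** The Study outcome measures section makes brain volume change at two years the primary endpoint and ties it to Hypothesis 1. The Sample size section states what that endpoint needs: "The primary endpoint requires a direct comparison of two groups: type 2 diabetes patients with LVH and those without".

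Under Hypothesis 1 the Statistical analysis section offers three analyses of volume:

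- **Per visit:** "Independent samples t-tests will be used to determine differences between participants with and without LVH at each time-point".
- **Within group, then compared:** "Repeated-measures t-tests will be used to determine the extent of brain volume loss across the two time-points. These results will be compared between groups".
- **A model:** "total brain volume, regional white matter, cortical and subcortical volume changes will be modelled using a repeated measures design".

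Intracranial volume is to be controlled in the analysis of regional brain volume change; total brain volume is not mentioned there. Hypothesis 3 repeats the second form (paired t-tests, then a comparison between groups) for left ventricular geometry.

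On sizing, the article states: "We used an ANCOVA method to estimate sample size for four samples". The four samples are LVH status crossed with cognitive impairment, with a baseline to follow-up correlation of 0.1, two-sided alpha 0.05 and 80% power. The only ANCOVA named in the Statistical analysis section is for laboratory data and left ventricular systolic function.

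**The concern.** The endpoint is a difference between two groups in change over time. A t-test at one visit compares levels, so it mostly reflects how much brain size varies between people. A paired t-test answers whether a group lost volume, not whether one group lost more than the other. The sentence that bridges to the group comparison, "These results will be compared between groups", names no test or estimator. The repeated measures model could supply the right quantity, but the text gives it no LVH term, no LVH-by-time contrast and no primary status.

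The primary conclusion could therefore rest on any of several analyses with very different properties. A real difference in atrophy could be missed by the per-visit tests. A difference could also be claimed, or dismissed, from two within-group results that do not test it. The stated power belongs to none of these analyses.

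**Working it through.** **1. The plan's own figure.** The 140 evaluable participants (35 in each of four groups) cannot be reproduced, because the article gives neither an LVH versus non-LVH difference nor an SD. What 140 implies can be back-solved. With 70 per LVH group, two-sided alpha 0.05 and 80% power, the detectable difference in SDs of a single volume measurement is

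d = (1.96 + 0.84) × √(2/70) × k,

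with k = 1 for a 24-month t-test, √(1 − r²) for ANCOVA and √(2(1 − r)) for a test on change.

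| r | 24-month t-test | ANCOVA | Change |
|---|---|---|---|
| 0.1 (plan) | 0.474 | 0.471 | 0.635 |
| 0.9 (assumed) | 0.474 | 0.206 | 0.212 |

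So the cost of the per-visit test depends on r. At r = 0.1 it loses almost nothing against ANCOVA. At r = 0.9 its detectable difference is more than twice that of either analysis that uses baseline.

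**2. Per-visit test against a direct test of change.** Inputs from the article: 168 recruited and 20% attrition, so 168 × 0.8 = 134.4, or 67 per LVH group. Assumed, because the article gives none of them: a 1-percentage-point difference in two-year loss, a between-person SD of volume of 4% to 10%, and an SD of change of 1 to 2 points. Power is from the noncentral t with noncentrality d × √(67/2).

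| Test | SD | d | Noncentrality | Power |
|---|---|---|---|---|
| 24-month t-test | 4 | 0.25 | 1.45 | 30% |
| 24-month t-test | 10 | 0.10 | 0.58 | 9% |
| Change | 2 | 0.50 | 2.89 | 82% |
| Change | 1.5 | 0.67 | 3.86 | 97% |
| Change | 1 | 1.00 | 5.79 | >99% |

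The correlation that these SDs imply, taking equal variance at both visits, is r = 1 − SD_change² / (2 × SD²):

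- SD 4 and SD of change 2: 1 − 4/32 = 0.875.
- SD 10 and SD of change 1: 1 − 1/200 = 0.995.

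The comparison therefore describes highly correlated volumes, not the plan's r = 0.1.

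**3. Side-by-side paired tests.** Suppose both groups have the same true change, with 70 per group. If each paired test has power p, exactly one is significant with probability 2p(1 − p).

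| Within-group standardised change | p | Exactly one significant |
|---|---|---|
| 0.20 | 0.378 | 47% |
| 0.25 | 0.541 | 50% |
| 0.34 | 0.801 | 32% |
| 0.50 | 0.985 | 3% |

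When within-group change is large, the fault is the reverse. With an assumed loss of 1% or 2% and an SD of change of 1.5 points (standardised change 0.67 or 1.33), each paired test has about 100% power. Both are then significant whether or not LVH matters.

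**4. Matching the sizing.** The sizing method is an ANCOVA across four groups defined by LVH and cognitive impairment. The primary contrast is between two groups, on change. No brain-volume ANCOVA is listed under Hypothesis 1, and a two-group ANCOVA would not be the sizing analysis either.

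**The case against.** The strongest reply is that the right analysis is already there. In a paragraph about comparing participants with and without LVH, total brain volume change is to be modelled with repeated measures. With two groups and two visits, the LVH-by-time term of that model is the difference in change. The sentence on comparing results between groups can also be read as comparing mean loss, and nothing says that two p-values will be set side by side. This stands. A reader might infer that the plan cannot estimate the LVH difference in change, or that it commits to judging by within-group significance. The text supports neither reading.

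A reader might also take the plan's r = 0.1 to show that a change score is much weaker than ANCOVA, and add that to the weakness of the per-visit test. The two cannot be combined. At r = 0.1 the per-visit test is nearly as good as ANCOVA, and at high r the change score is. Nor do the groups' non-randomised origin and an endpoint defined as change make ANCOVA the clear first choice.

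Finally, a condensed article may leave the confirmatory model term to an analysis plan that is not shown. That lowers the weight of the point but does not remove it. The article does name tests for its primary hypothesis, and those named most explicitly either compare levels or stop short of the between-group comparison that its own Sample size section requires.

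**Conclusion.** The point holds as a failure to name and rank. Hypothesis 1 lists per-visit t-tests, paired t-tests with an unnamed between-group step, and a repeated measures model with no stated contrast. None is identified as the test of the primary endpoint, intracranial volume control is stated only for regional change, and none corresponds to the sizing ANCOVA.

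The harm is conditional: it arises if the t-tests carry the conclusion. In that case power is about 30% to 9% for the 24-month test against 82% or more for a direct test of change. This rests on the assumed 1-point difference and SDs given above, none of which is in the article, and on highly correlated volumes. That side-by-side paired results are not a valid test of the difference needs no such assumption.

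**What to change.** - Make the LVH versus non-LVH difference in two-year total brain volume change the single primary contrast. Estimate it with a 95% CI by the LVH-by-time term of the repeated measures model already planned, which with two visits and complete data is the between-group comparison of mean change.
- State how intracranial volume enters for total brain volume. As a main effect only, it leaves the LVH-by-time estimate unchanged in complete data, so it should act on change (an intracranial-volume-by-time term, or normalised volumes).
- Give the baseline-adjusted ANCOVA as a supporting analysis, because the groups are not randomised and the two approaches can differ when baseline volumes differ.
- Label the per-visit and within-group t-tests as descriptive, and use the same form for Hypothesis 3.
- State that the four-group ANCOVA with r = 0.1 does not correspond to this contrast, and restate the power basis with a difference and an SD of change. As a guide, an assumed 1-point difference needs 16, 36, 63 or 142 per group for an assumed SD of change of 1, 1.5, 2 or 3 points.

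The cost is minor rewording of the analysis and sample size text. MRI at both visits is already in the schedule of assessments, so no new measurement is needed.
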